## Abstract

**Introduction::**

Acupuncture and moxibustion has become a commonly used adjuvant treatment method to improve the success rate of in vitro fertilization-embryo transfer (IVF-ET). However, There is still insufficient evidence that acupuncture treatment can improve the local microenvironment of endometrium, the endometrial receptivity, and the pregnancy outcome of patients, which is worthy of further study.

**Method/Design::**

To investigate the effect of Stage by Stage Acupuncture and Moxibustion Therapy on endometrial receptivity and Pregnancy Outcome based on the theory of “Chong channel being sea of blood,” we will conduct a multicenter randomized controlled trial. Inclusion criteria are as follows: infertile women under 45 years of age who received IVF-ET or Intracytoplasmic sperm injection cycles. The study will only be applied to women who have failed repeated implantation, that is, women who have failed 3 or more embryo transplants in the past (existing frozen embryos do not require the retrieval of eggs). Those who are not prepared to receive IVF-ET or are at risk of pregnancy, have a serious medical condition, or are egg donors will be excluded. Subjects will be randomly assigned to either the acupuncture group (IVF-ET plus stage-by-stage acupuncture and moxibustion therapy based on the “Chong channel being sea of blood” theory) or the control group (IVF-ET only). The trial required a total sample size of 246 women to compare endometrial receptivity between the 2 groups. The acupuncture group will receive acupuncture and moxibustion treatment 3 times a week starting from the third day of menstruation in the ovary stimulation cycle. One menstrual cycle was one course of treatment, and a total of 3 menstrual cycles were treated. The main outcome indicator was clinical pregnancy rate. Secondary outcome indicators were the three-dimensional volume blood flow parameters (vascularization index, flow index, and vascularization flow index) of the endometrium, endometrial thickness, endometrial volume, uterine artery PI, RI, and S/D during the “implantation window period” (20–24 days after menstruation in the ovary stimulation cycle).

**Discussion::**

This study will provide important evidence for the use of Stage by Stage Acupuncture and Moxibustion Therapy Based on the “Chong Channel Being Sea of Blood” Theory in IVF.

**Trial registration::**

http://www.chictr.org.cn/edit.aspx?pid=28811&htm=4 ID: ChiCTR1800017191 (07/17/2018).

## Introduction

1

Infertility, together with malignant tumors and cardiovascular diseases, has been listed as 1 of the 3 major diseases affecting the quality of human life.^[1]^ With the opening up of China's 2-child policy and the continuous increase of fertility requirements, the number of elderly mothers is increasing, infertility has become a serious social problem.^[2]^ In vitro fertilization—embryo transfer has become the most effective treatment of infertility. Although in vitro fertilization-embryo transfer (IVF-ET) has been in operation for nearly 30 years since the birth of the world's first IVF baby in 1978, the clinical pregnancy rate remains at only 30%.^[3]^ The latest research shows that two-thirds of the reasons for implantation failure of IVF-ET embryos are due to insufficient endometrial receptivity, endometrial receptivity is closely related to embryo implantation.^[4]^ For IVF-ET patients who failed for 3 times or more, improving endometrial blood perfusion to create a microenvironment suitable for embryo implantation is the most effective way to increase clinical pregnancy.^[5]^ In recent years, acupuncture has shown a good momentum in the application of IVF-ET. The latest meta-analysis shows that acupuncture or acupuncture combined with other therapies can improve the endometrial receptivity of IVF-ET patients.^[6]^ However, the existing researches on acupuncture and moxibustion are generally of heterogeneity, especially in the aspects of acupuncture and moxibustion treatment methods and acupoint selection, currently there is no recognized treatment reference standard, which makes the clinical effect very different,^[7]^ and there are too many studies on acupuncture and moxibustion combined with other therapies to clearly prove the efficacy of acupuncture and moxibustion. In the 19 years of clinical practice, we have formed the stage-by-stage acupuncture and moxibustion therapy for the treatment of female infertility. Previous studies have found that stage-by-stage acupuncture and moxibustion therapy based on the “Chong channel being sea of blood” Theory can increase the thickness of the endometrium in the middle luteal stage of IVF-ET patients with repeated failure of transplantation, and improve the clinical pregnancy rate.^[8]^ Preliminary experiments have shown that the acupuncture therapy can improve the blood flow parameters under the endometrium. To this end, we plan to conduct a more rigorous large-scale multicenter randomized controlled trial to further evaluate the effectiveness of stage-by-stage acupuncture and moxibustion therapy based on the “Chong channel being sea of blood” theory to improve endometrial receptivity and pregnancy outcome.

## Method/design

2

This study was designed as a multicenter, randomized, parallel controlled, double-blind trial of evaluators and statisticians. Participants will include the following 3 hospitals: Yunnan first people's hospital, Yunnan second people's hospital, and Yunnan provincial hospital of traditional Chinese medicine. Every research center must strictly follow the inclusion and exclusion criteria. The study will be conducted in the following order: patients will be screened and qualified for enrollment, they will be randomly assigned to receive acupuncture 3 times a week, 1 menstrual cycle for 1 course of treatment, a total of 3 menstrual cycles, and a 40-week follow-up period. The research plan has already been clinical trials of traditional Chinese medicine hospital ethics committee approval in Yunnan province, China (grant no. (2017) (032)—01), and registered on the Chinese clinical trial registry (http://www.chictr.org.cn/, ID: ChiCTR1800017191). This study will adhere to the Standard Protocol items: Recommendations for Interventional Trials (SPIRIT) 2013 statement(see Fig. 1 for the SPIRIT figure of enrollment, interventions, and assessments). Every participant will sign an informed consent form. Patients will be enrolled in the study and will be recruited only once and will not receive any financial compensation for their participation in the study.

**Figure 1 F1:**
[figure not shown]
The SPIRIT figure of enrollment, interventions, and assessments. SPIRIT = indicates standard protocol items recommendations for interventional trials.

### Eligibility criteria

2.1

Women admitted to the reproductive medicine center of the research hospital will be screened to determine their suitability for in vitro fertilization. All IVF indications for women, such as tubal infertility, severe male factor infertility, endometriosis, unexplained infertility, immune infertility, and anovulation infertility, were recommended for this study. The included patients must be infertile women under the age of 45 who have undergone in vitro fertilization-embryo transfer or Intracytoplasmic sperm injection cycles, who have experienced 3 or more IVF-ET failures, and who have frozen embryos and no longer need to take eggs. Exclusion criteria were severe physical diseases or contraindications to acupuncture and moxibustion, poor pregnancy and birth history, thrombotic diseases, etc.

Patients have the right to refuse to participate in the study, and they can withdraw at any time. Their consent or withdrawal would not affect their intended IVF treatment.

### Sample size

2.2

Based on the calculation of sample size, 2 groups are proposed in this scheme. Test level α=0.05, test efficiency 1−β= 0.90. The retention rate of acupuncture and moxibustion group was based on the effective rate of acupuncture in stages on endometrial receptivity in our previous research results (27%),^[8]^ and the effective rate of subendometrial blood flow parameters in the study of acupuncture in enhancing endometrial receptivity (26.3%) in Hu et al,^[9]^ which was estimated to be 27%. In the meta-analysis based on Smith et al, the effective rate of the blank group was 10%.^[10]^ Therefore, 10% of the control group was selected as the minimum clinical test difference that might change clinical practice. In the staged acupuncture group, 27% was the smallest difference in clinical detection that could change clinical practice, and the shedding rate was 10%. According to the formula $n=\frac{1}{\left(1-f\right)}*\left[\frac{2*{\left(z_{\alpha }+z_{\beta }\right)}^{2}*p*(1-p)}{\left(p_{0}-p_{1}\right)}\right],\;\;\;\;\;p=\frac{\left(p_{0}-p_{1}\right)}{2}$,^[11]^ where n= the sample size of each group. F = shedding rate, value 0.1. P0 = effective rate of the control group, with a value of 0.1. P1 = effective rate in the stage acupuncture group, with a value of 0.27. Z_α_ = 1.65 when α=0.05 (unilateral). When 1−β = 0.90, Z _β_ = 1.28. After calculation, n = 122.12≈123. Finally, the sample size of each group was taken as 123 cases.

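### The inputs stated in Sample size (2.2) give 100 per arm, not 122.12, and the text does not show which input is wrong

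*Protocol article*

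**What the plan says.** Section 2.2 of the protocol article sets the error rates ("Test level α=0.05, test efficiency 1−β= 0.90") and gives the normal quantile for alpha as "1.65 when α=0.05 (unilateral", that is, one-sided. The quantile for power is "When 1−β = 0.90, Z _β_ = 1.28". The remaining inputs are:

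- "P0 = effective rate of the control group, with a value of 0.1"
- "P1 = effective rate in the stage acupuncture group, with a value of 0.27"
- "F = shedding rate, value 0.1"

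The printed formula is n = [1/(1−f)] × [2(Zα+Zβ)² p(1−p) / (p0−p1)], with p = (p0−p1)/2 and n the size of each group. The result is "After calculation, n = 122.12≈123". Section 2.4.1 then randomises 123 to each arm, 246 in total. Section 2.8 names t and chi-square tests and refers to significant effects, but does not say whether the tests are one- or two-sided.

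**The concern.** The article prints its formula, every input and the result, so the calculation can be repeated, and it does not come out. Half the difference of two rates is not a pooled proportion; here it is negative. The usual formula squares the difference in the denominator. The one-sided quantile of 1.65 also looks too small to lead to 123 per arm with these rates.

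Two things are at stake. First, the basis for 246 women cannot be verified. Second, section 2.2 holds the article's only statement of sidedness, and its own result is inconsistent with the inputs that go with that statement. The false-positive risk in favour of acupuncture is 5% under a one-sided 5% test and 2.5% under a two-sided 5% test. A one-sided p-value between 0.025 and 0.05 would be a success under the first and not under the second. Patients and acupuncturists are not blinded (2.4.2), so this threshold should be beyond doubt before results are seen.

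**Working it through.** **Inputs, all from 2.2:** p0 = 0.10, p1 = 0.27, f = 0.10, Zα = 1.65, Zβ = 1.28. Hence (Zα+Zβ)² = 2.93² = 8.5849.

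**1. Formula as printed.** p = (0.10 − 0.27)/2 = −0.085, so p(1−p) = −0.085 × 1.085 = −0.092225.
n = (1/0.9) × 2 × 8.5849 × (−0.092225)/(−0.17) = 10.35 per arm. The result is positive only because two negative signs cancel.

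**2. Formula repaired, stated inputs kept.** p = (0.10 + 0.27)/2 = 0.185, p(1−p) = 0.185 × 0.815 = 0.150775, denominator 0.17² = 0.0289.
n = (1/0.9) × 2 × 8.5849 × 0.150775/0.0289 = 89.58/0.9 = 99.53, so 100 per arm.
Repairing only one slip does not help: 16.9 with p alone corrected, and 51.3 with the denominator alone squared and |p| = 0.085.

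**3. Other standard methods, one-sided, after 10% loss.** Unpooled variance 94.8; arcsine 94.5; Fleiss 98; Fleiss with continuity correction 110; Fisher exact 107. None reaches 122.12.

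**4. Two-sided 5%, Zα = 1.96.** (1.96 + 1.28)² = 10.4976.
n = (1/0.9) × 2 × 10.4976 × 0.150775/0.0289 = 109.53/0.9 = 121.71, so 122. With Zβ = 1.2816 it is 121.82. Both are close, but neither is 122.12, and neither rounds up to 123. Other two-sided methods give 115.9 (unpooled), 115.6 (arcsine), 120 (Fleiss), 134 (Fleiss with continuity correction) and about 128 (Fisher exact).

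**5. A different rate, one-sided.** The only other acupuncture rate in 2.2 is 26.3%. It gives 106.7 one-sided and 130.4 two-sided, so it does not explain the figure. As a sensitivity input only, take p1 = 0.25 (an assumption, not in the document). Then p = 0.175, p(1−p) = 0.144375 and the denominator is 0.15² = 0.0225.
- With the printed 1.65 and 1.28: (1/0.9) × 2 × 8.5849 × 0.144375/0.0225 = 122.41, which rounds up to 123.
- With unrounded quantiles (1.6449 and 1.2816, squared sum 8.5638): 122.11.

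**6. What 123 per arm delivers for 10% v 27%.** After 10% loss, 123 × 0.9 = 110.7, about 111 per arm. The standard error is √(2 × 0.150775/111) = 0.05212 under the null and √((0.09 + 0.1971)/111) = 0.05086 under the alternative.
- Two-sided 5%: (0.17 − 1.96 × 0.05212)/0.05086 = 1.334, power 90.9%.
- One-sided 5%: (0.17 − 1.645 × 0.05212)/0.05086 = 1.657, power 95.1%.

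**The case against.** The two formula slips are probably misprints. The standard formula is recognisable, a negative p is meaningless, and 122.12 cannot have come from the expression as printed. The figure of about 10 per arm therefore describes a typographical fault and not a design that anyone used. That stands. It does not rescue the result, because the repaired formula with the stated inputs still gives 100.

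It is also fair to say that the practical consequence is small. The planned number exceeds what the stated one-sided design needs, and it meets 90% power two-sided as well. The gap of 23 per arm is a surplus. A reader who infers from the faulty arithmetic that the trial is underpowered for 10% v 27% would be wrong.

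A second tempting inference is that 123 must come from a two-sided test, so that the one-sided wording is the mistake. The documents do not support this. The two-sided calculation misses both the raw and the rounded figure, while a one-sided test with a rate near 0.25 comes within 0.01 of 122.12 with unrounded quantiles and gives 123 with the printed ones. That rate is only an assumption, but it shows that the wrong input could be the rate and not the sidedness.

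Third, sidedness may be fixed in an analysis plan that is not shown, and section 2.8 does not say that success will be claimed at one-sided 5%. An inflated error rate is thus a possibility and not something that the article lays down. The silence of 2.8 is not itself the fault; the fault is that 2.2 states a sidedness and a result that do not fit together.

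**Conclusion.** Section 2.2 is wrong as written. Its stated inputs require 100 per arm (200 in total) and not 123 (246), so the plan is 23% above its own stated need. The printed formula cannot produce either number. Which input differs from the one actually used cannot be determined from the text: two-sided 5% with a rate of 0.27 gives 121.7, and one-sided 5% with an assumed rate of 0.25 gives 122.1.

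The consequences are a justification that cannot be reproduced and an unclear success threshold (5% or 2.5% false-positive risk in favour of acupuncture). Loss of power is not among them: 123 per arm give about 91% two-sided or 95% one-sided. These power figures take the rates of 10% and 27% and the 10% loss as stated, and use the normal approximation.

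**What to change.** In 2.2, define p as (p0+p1)/2 and square the denominator. Recover the original calculation and state the rates and sidedness that were actually used, with a result that follows from them. Make 2.2 and 2.8 state the same sidedness.

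Keep 123 per arm and report what it delivers for 10% v 27% with about 111 evaluable per arm: about 91% power at two-sided 5%, or about 95% at one-sided 5%. If one-sided 5% is really intended, say so, give a reason for it, and explain why 123 are randomised when 100 would do. Two-sided 5% is the conservative choice: it fits the existing number and keeps power above the stated 90%. Its only cost is a somewhat lower stated power, 91% instead of 95%.

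The change is to the text alone. Recruitment and the total of 246 are unaffected. The sidedness should be settled before any comparison by group is seen.

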### Recruitment and registration methods

2.3

At present, a large number of infertility patients are seeking treatment in the Yunnan First People's Hospital, Yunnan Second People's Hospital, and Yunnan Provincial Hospital of Traditional Chinese Medicine. Patients will participate in the trial mainly through the recruitment poster of the reproductive center of the relevant hospital.

Patients of interest will be screened by specific researchers who are familiar with the inclusion and exclusion criteria for the study. Participants will have a clear and comprehensive understanding of the trials they will participate in, such as the benefits they may gain, the potential risks, the setup of the trial group, and the interventions they will undertake. We will pay particular attention to baseline characteristics such as age, cause and duration of infertility, ethnic distribution, history of smoking or drinking, history of exposure to radiation or chemotherapy, repeated IVF implantation failure, endometrial disease (inflammation, ectopic), and previous pelvic surgery. Patients who are willing to participate and meet the eligibility criteria will be referred to the acupuncture and moxibustion therapists participating in the study.

### Principles of randomness and blindness

2.4

#### Randomly assigned

2.4.1

This is a multicenter, randomized, controlled trial in 3 Chinese hospitals. The central randomization was carried out by Yunnan Provincial Hospital of traditional Chinese medicine, and the pseudo-random numbers were generated by “computer pseudo-random number generation method.” Then the patients represented by the random numbers in the even-numbered position in the sorting list were included in the acupuncture and moxibustion group, and the rest were included in the control group. Two hundred forty-six patients who met the inclusion criteria were randomly divided into 123 patients in the control group (IVF-ET only) and 123 patients in the acupuncture group (IVF-ET plus stage-by-stage acupuncture and moxibustion therapy based on the “Chong channel being sea of blood” theory). Randomized assignments to the acupuncture or control groups will be generated by independent researchers using computer software. Computer-generated treatment codes will be placed in sealed, opaque envelopes, and distributed by dedicated study nurses, who will be trained before the trial and will not participate in treatment or care. The basic principles of randomization are as follows: the researchers cannot predict the allocation of patients, and there will be no change in the allocation after randomization.

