### Statistical analysis

2.8

SPSS v. 21.0 Windows was used for statistical analysis. All data are presented as mean ± standard deviation or percentage. Independent samples were compared using the *t* test. Descriptive statistics and bivariate tests (e.g., correlation test, *t* test, and *χ*^2^ test) will be used to summarize the sample demographics and to examine the distribution characteristics and relationships of the study results. Specifically, we will assess the overall difference (group effect) in endometrial three-dimensional volume blood flow parameters (VI, FI, and VFI) between the acupuncture group and the control group, changes during the study period (time effect), and differences in such changes (intergroup interaction) between the groups. Significant group effects or intergroup interactions will indicate significant effects of the intervention.

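### Allocation is balanced overall but not within the three hospitals, and the stated comparison of clinical pregnancy uses neither hospital nor recorded baseline prognosis: a modest, cheaply recovered loss of precision

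*Protocol article*

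**What the plan says.** Section 2.4.1 of the protocol article sets the trial in three hospitals ("This is a multicenter, randomized, controlled trial in 3 Chinese hospitals") and states that "The central randomization was carried out by Yunnan Provincial Hospital of traditional Chinese medicine". Computer pseudo-random numbers are generated and sorted. Then "the patients represented by the random numbers in the even-numbered position in the sorting list were included in the acupuncture and moxibustion group", with the rest forming the control group. The result is given only in total, the second figure being the acupuncture arm: "Two hundred forty-six patients who met the inclusion criteria were randomly divided into 123 patients in the control group (IVF-ET only) and 123 patients". No stratum, block or minimisation factor is named. That one list serves all three hospitals is an inference from the singular list, the central generation and the single overall split; the text does not say so outright. The same section says that treatment codes go into sealed opaque envelopes and that "the researchers cannot predict the allocation of patients".

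Section 2.3 lists factors to be recorded at baseline: "We will pay particular attention to baseline characteristics such as age, cause and duration of infertility", and it also names repeated implantation failure. Section 2.6 makes clinical pregnancy the main outcome. Section 2.8 relies on "Descriptive statistics and bivariate tests", with correlation, t and chi-square tests as examples, and adds a group, time and group-by-time assessment for the blood flow parameters VI, FI and VFI. It names no test for clinical pregnancy as such; of those listed, chi-square is the one that fits a binary outcome. Neither hospital nor any baseline factor is named in an analysis.

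**The concern.** The even-position rule guarantees equal totals but lets the arms differ in size within a hospital. Hospital could matter here because each site has its own two acupuncturists (section 2.5). If pregnancy rates differ between sites, uneven arms within sites add chance variation to the treatment difference, and an unadjusted chi-square test leaves that variation in. The same holds for any recorded baseline factor that predicts pregnancy. At stake is precision in the primary comparison, which adjustment for data already collected could recover.

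**Working it through.** **Inputs from the protocol article.** N = 246, 123 per arm, three hospitals (2.4.1). Rates 0.10 and 0.27, dropout 0.10, and "Test level α=0.05, test efficiency 1−β= 0.90" (2.2). Hospital sizes and hospital pregnancy rates are not given, so they are assumed below.

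**The plan's own sample size.** With mean rate (0.10 + 0.27)/2 = 0.185, a squared difference in the denominator and two-sided z = 1.96:

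n = [2 × (1.96 + 1.28)² × 0.185 × 0.815 / 0.17²] / 0.9 = 109.53 / 0.9 = 121.7, close to the stated 122.12.

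The one-sided 1.65 given in section 2.2 leads to 99.5. That discrepancy is a separate matter. Two-sided 0.05 is used below because it is what 123 per arm corresponds to.

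**Step 1: imbalance within a hospital.** If 123 of 246 list places are acupuncture, the number of acupuncture patients in a hospital enrolling m women is hypergeometric (246, 123, m), with variance m × ¼ × (246 − m)/245. For m = 82 this is 82 × 0.25 × 164/245 = 13.72, a standard deviation of 3.70.

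| Hospital size (assumed) | 95% range in acupuncture | Chance of 60:40 or worse |
|---|---|---|
| 82 (equal thirds) | 34 to 48 | 2% |
| 60 | 23 to 37 | 10% |
| 40 | 14 to 26 | 23% |

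In simulation (40,000 runs), the chance that at least one hospital has arms differing by 10 or more is 44% for sizes 82/82/82, 35% for 123/73/50 and 36% for 148/62/36.

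**Step 2: effect on the comparison.** Clinical pregnancy was simulated (40,000 runs, no dropout) with a common odds ratio of (0.27/0.73)/(0.10/0.90) = 3.33. The unadjusted chi-square test was compared with a Cochran-Mantel-Haenszel (CMH) test stratified by hospital.

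| Sizes | Control rates, % | Single list, unadjusted: power % | Single list, CMH: power % | Stratified list, CMH: power % |
|---|---|---|---|---|
| 82/82/82 | 10/10/10 | 94.31 | 93.85 | 94.05 |
| 82/82/82 | 5/10/15 | 92.79 | 93.04 | 93.34 |
| 82/82/82 | 4/10/20 | 92.70 | 93.83 | 94.16 |
| 82/82/82 | 15/30/45 | 98.72 | 99.22 | 99.35 |
| 122/74/50 | 10/10/10 | 94.36 | 93.95 | 93.99 |
| 122/74/50 | 5/10/15 | 89.36 | 89.70 | 90.14 |
| 122/74/50 | 4/10/20 | 87.81 | 89.44 | 89.79 |
| 122/74/50 | 15/30/45 | 98.60 | 99.06 | 99.18 |

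The largest gap between the first and last power columns is 89.79 − 87.81 = 1.98 points. Of that, 89.44 − 87.81 = 1.63 points come from the analysis alone, without changing the list. With no hospital differences nothing is gained, and CMH gives up 94.31 − 93.85 = 0.46 points or 94.36 − 93.95 = 0.41 points.

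**Step 3: bias and type I error.** The unadjusted test on the single list rejects a true null in 4.8% to 5.1% of runs over all eight settings. The 95th percentile of the chance difference between arms due to hospital is 1.5 to 1.7 percentage points for control rates 4/10/20% and about 3 points for 15/30/45%. The planned difference is 17 points.

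**The case against.** The best defence is that this is a condensed article, and that adjustment for hospital and covariates is commonly left to the analysis plan or full protocol. Section 2.8 is silent on hospital and age; it does not exclude them. That stands: the omission is not an error, and the point is only that the comparison as stated can be improved. It is also fair that unstratified randomisation of 246 women over three hospitals is legitimate, that equal hospitals make a bad split unlikely (2%), and that the article standardises much: one stimulation regimen, uniformly trained acupuncturists, and scans at one setting by one person. It gives no evidence that pregnancy rates differ by hospital. Nor is section 2.8 bivariate throughout, since VI, FI and VFI get a group-by-time assessment.

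Three stronger readings are tempting, and the text does not support them.

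- *Strict alternation.* A reader might take even positions to mean every second woman enrolled, which would make each next allocation known. But the rule concerns random numbers in a sorted list, and the section adds independent computer generation, opaque envelopes and an explicit principle against prediction. The natural reading is a sort by random number. The sort key could be stated more clearly, and no more than that.
- *Conflict between central randomisation and envelopes.* Generating a list centrally and then concealing it in envelopes is one coherent procedure.
- *Bias.* Chance imbalance within hospitals adds variation. It does not bias a valid random split, and the simulation shows no inflation of type I error.

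**Conclusion.** The point holds as a design improvement of low to moderate importance. The allocation as naturally read is valid. It balances arms only in total, and the tests named for the primary outcome use neither hospital nor recorded prognosis. The price is possible imbalance within hospitals and about 0 to 2 points of power, with no effect on validity. These sizes rest on assumed hospital sizes and pregnancy rates and on the inference that one list serves all sites. The value of adjusting for age or previous failed transfers was not quantified, because the document gives no figures for their effect. The conclusion would lapse if the analysis plan, not shown, already adjusts the primary comparison.

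**What to change.** Make the primary analysis of clinical pregnancy a comparison adjusted for hospital and age, and for number of previous failed transfers where recorded: for example a logistic model reporting an adjusted risk difference, or at least a CMH test by hospital, in place of an unadjusted chi-square test. Fix the covariates before group codes are opened. This needs a wording change, no new data and no change to the sample size. The only price seen is up to about half a point of power if hospitals do not differ.

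State in section 2.4.1 that the list is sorted by random number; this takes one sentence.

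Optionally, if recruitment is still open, allocate the remaining women by permuted blocks of varying size stratified by hospital. This costs a short amendment and two list versions to document. In the simulation it added at most 90.14 − 89.70 = 0.44 points of power beyond CMH on the single list, so the adjusted analysis is the priority. If the list is stratified, the analysis should include hospital: with the unadjusted test on a stratified list, simulated type I error fell as low as 4.2%, which makes the test conservative.
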